## Abstract

**Background:** Healthy cognitive functioning is a primary component of well-being, independence, and successful aging. Cognitive deficits can arise from various conditions, such as brain injury, mental illness, and neurological disorders. Rehabilitation is a highly specialized service limited to patients who have access to institutional settings. In response to this unmet need, telehealth solutions are ideal for triggering the migration of care from clinics to patients’ homes. **Objectives:** The aim of EARLY-COGN^3 will be threefold: (1) to test the efficacy of a digital health at-home intervention (tele@cognitive protocol) as compared to an unstructured cognitive at-home rehabilitation in a cohort of patients with Chronic Neurological Diseases (CNDs); (2) to investigate its effects on the biomolecular and neurophysiological marker hypothesizing that people with CNDs enrolled in this telerehabilitation program will develop changes in biological markers and cortical and subcortical patterns of connectivity; (3) to analyze potential cognitive, neurobiological, and neurophysiological predictors of response to the tele@cognitive treatment. **Method:** In this single-blind, randomized, and controlled pilot study, we will assess the short- and long-term efficacy of cognitive telerehabilitation protocol (tele@cognitive) as compared to an unstructured cognitive at-home rehabilitation (Active Control Group—ACG) in a cohort of 60 people with Mild Cognitive Impairment (MCI), Subjective Cognitive Complaints (SCCs), or Parkinson’s Disease (PD). All participants will undergo a clinical, functional, neurocognitive, and quality of life assessment at the baseline (T0), post-treatment (5 weeks, T1), and at the 3-month (T2) follow-up. Neurophysiological markers and biomolecular data will be collected at T0 and T1. **Conclusions:** EARLY-COGN^3 project could lead to a complete paradigm shift from the traditional therapeutic approach, forcing a reassessment on how CNDs could take advantage of a digital solution. (clinicaltrials.gov database, ID: NCT06657274)

## 1. Introduction

Dementia is currently a public health priority at the center of the global action plan (2017–2025), requiring new solutions to support patients and families in managing disabilities related to the disease [1]. The world’s population is aging, requiring us to face new challenges. Improvements in medical care have led to a consistent increase in the average age, and it is estimated that the elderly population will increase again. Healthy cognitive functioning is a primary component of well-being, independence, and successful aging. In this context, the importance of prompt intervention with rehabilitation on residual capabilities is well known. However, rehabilitation remains a highly specialized service for a limited number of subjects with access to an institutional setting [2]. In response to this unmet need, telehealth solutions are ideal for triggering the migration of care from clinics to individuals’ homes and, consequently, scaling up cognitive rehabilitation from a limited number of participants to a broader range of targets [3]. The need for alternative kinds of dementia service delivery is increasing because of the growing demand and cost of healthcare; the rapid development of technology could meet this need. In particular, equitable access to services, improvement of quality of care, and the promotion of self-management are benefits to be delivered from telerehabilitation.

The increase in life expectancy in recent decades has led to a large number of people living into old age, alongside an increased risk of developing Chronic Neurological Diseases (CNDs), such as neurodegenerative diseases [4,5,6]. A higher cumulative risk of dementia has been widely demonstrated in Mild Cognitive Impairment (MCI) and Subjective Cognitive Complaints (SCCs) subjects, and in Parkinson’s Disease (PD) patients, as compared to the general population [7,8,9]. As the disease progresses, individuals become increasingly dependent on medical services and family support. SCCs condition is defined based on self-reports regarding complaints of cognitive decline, often of memory, although normal functioning can be detected on objective tests [10,11]. The concept of SCCs is highly significant to the field of aging because this condition is a risk factor for developing dementia [11,12,13,14,15]. The diagnosis of MCI requires both subjective cognitive complaints and objective impairment in at least one area of cognition [16,17]. Given the increased risk of developing Alzheimer’s Disease (AD) in these populations [11], there is a strong argument for developing effective interventions aimed at reducing cognitive decline in MCI and SCCs. Regarding patients with PD, one of the most common age-related brain disorders, it is defined primarily as a movement disorder, with typical symptoms including resting tremor, rigidity, bradykinesia, and postural instability [18,19,20]. However, a range of non-motor symptoms emerge throughout the course of the disease, such as cognitive decline and mood disturbances [21]. In terms of cognitive deficits, a meta-analysis has reported that cognitive training could potentially help to attenuate cognitive deficits in patients with PD [22].

There have been recent arguments for a beneficial effect of non-invasive treatments such as cognitive programs in SCCs, MCI, and PD [23,24,25,26]. Given the limited effectiveness of pharmacological treatments, attention has been focused in recent years on non-pharmacological interventions aimed at preventing and treating cognitive deficits, as well as the associated difficulties with activities of daily living in individuals with neurodegenerative diseases. Among these, cognitive training offers a potential approach for dementia prevention and cognitive function improvement [27,28,29,30,31,32,33]. A critical aspect of cognitive training programs is that the most promising interventions have involved intensive in-person sessions that are unlikely to be cost-effective or feasible for large-scale implementation [34]. Within the framework of non-pharmacological interventions, the use of technology to assist at-home people at risk of or with mild dementia has gradually gained importance [3,35]. Telerehabilitation technologies enable the provision of health services remotely, allowing participants living in rural areas or those with mobility difficulties access to healthcare [3,35,36,37,38,39,40,41,42,43,44,45,46,47,48,49,50,51,52,53,54]. Moreover, telerehabilitation offers the advantage of providing rehabilitation within the subject’s natural home environment, making the treatment more realistic and potentially more generalizable to the individual’s daily life [55].

Cognitive rehabilitation is a potential approach for improving cognitive function and delaying cognitive decline [22,27,28,29,56,57,58,59,60,61,62,63,64,65,66,67,68]. In the case of neurodegenerative disease, what makes the situation more challenging is that subjects are usually diagnosed and treated only after symptoms appear, typically 10–20 years after the initial pathological changes in the brain. This delay makes it difficult to counteract disease progression. Therefore, early rehabilitation has a crucial role in managing neurodegenerative conditions and it is extremely important to identify effective interventions capable of reducing the incidence of these disabilities in older adults with CNDs [69,70]. The potential benefits of telerehabilitation have been highlighted in the literature [71] and these technologies have been also applied to cognitive rehabilitation in individuals with neurodegenerative diseases or with subjective complaints [3,40,51,54,72,73], with the aim to prevent or delay the onset of CNDs [74]. The delivery of rehabilitation through various technologies can help overcome the limitations of high-intensity face-to-face (FTF) rehabilitation interventions [3,35,36,40,41,75]. The results of studies showing that telerehabilitation achieves comparable outcomes to traditional FTF services appear interesting [42,43,44,45,46,47,48,49,51,52,53,54,76,77,78,79], and two systematic reviews [38,51] reported that cognitive telerehabilitation has similar effects in terms of efficacy, validity, and reliability to that of conventional FTF rehabilitation. In a recent study, we observed that MCI subjects who had received FTF rehabilitation, followed by asynchronous tablet telerehabilitation, maintained improvements in memory at the 7-month follow-up [80]. This Randomized Clinical Trial (RCT) confirms the feasibility, patient adherence to treatment, and good usability of technology in subjects with MCI. These results are in agreement with recent findings and meta-analyses on the efficacy and feasibility of a cognitive telerehabilitation program in individuals with MCI [46,48,76,78,81,82,83,84]. Regarding PD, telemedicine could represent an emerging and innovative approach to support cognitive and behavioral rehabilitation, reducing the overload of healthcare facilities and promoting home-based therapy [40,77,85,86,87]. Additionally, the implementation of digital contents promotes engagement [88] and facilitates measurement of the patient’s performance and progress in terms of accuracy, reaction time, number of repetitions, and time spent in rehabilitative sessions.

Nevertheless, asynchronous models of telerehabilitation require a complex technological ecosystem underlying clinic–home communication, and, as a result, RCTs demonstrating the effectiveness of these solutions are still scarce [72,89]. However, no studies have been conducted to assess the feasibility and efficacy of cognitive rehabilitation delivered by digital therapeutics—an additional way to scale up cognitive rehabilitation—in older people with CNDs.

The neural bases of spontaneous and rehabilitation-induced recovery remain largely unknown. While there is substantial evidence that brain plasticity plays a role in overcoming cognitive deficits, until recently rehabilitation had been based only upon observational studies [90]. Within the emerging field of cognitive neuroscience, recent discoveries suggest that the central nervous system responds dynamically to insults, thus explaining that, at least in some cases, lost behaviors can be restored [91].

Many studies have investigated various cognitive, neurobiological, and neurophysiological predictors of response to rehabilitation intervention. However, a synthesis of this literature and an understanding of which cognitive, biological, and neurophysiological targets predict response is lacking. Neurophysiological response to Transcranial Magnetic Stimulation (TMS) and blood biomarkers of neurodegeneration, neuroinflammation, synaptic function, and neuronal communication might influence the efficacy of cognitive rehabilitative protocols based on a digital health at-home intervention [92].

In this single-blind, randomized, controlled pilot study, we will aim to: (1) test the short-term and long-term efficacy of a cognitive telerehabilitation protocol (tele@cognitive) as compared to an unstructured cognitive at-home rehabilitation (Active Control Group—ACG) in the treatment of a cohort of patients with SCCs, MCI, PD; (2) investigate its effects on the biomolecular and neurophysiological markers hypothesizing that people with CNDs enrolled in this telerehabilitation program will develop changes in biological markers and in cortical and subcortical patterns of connectivity; (3) analyze potential cognitive, neurobiological, and neurophysiological predictors of response to the tele@cognitive treatment.

In particular, the first aim will be to assess the short-term and long-term efficacy of tele@cognitive protocol as compared to an unstructured cognitive at-home rehabilitation in the treatment of a cohort of patients with CNDs, monitoring intervention effectiveness by a clinical, functional, neurocognitive, and quality of life assessment applied before treatment (T0), after treatment (5 weeks, T1), and at a 3-month follow up visit (T2). We hypothesize that this digital health at-home intervention would ameliorate cognitive abilities more than unstructured at-home rehabilitation in subjects with SCCs, MCI, and PD. We will also evaluate adherence to the rehabilitation program delivered at-home in the absence of therapist supervision. It is hypothesized that, at an early stage of the disease, cognitive telerehabilitation treatment with innovative digital solutions can bring about positive effects on treatment adherence and difficulties specific to each clinical condition.

The second aim will be to investigate the effects of a cognitive rehabilitative protocol based on a digital health at-home intervention (tele@cognitive) on biomolecular and neurophysiological markers, hypothesizing that people with CNDs enrolled in the tele@cognitive protocol will develop changes in circulating biomarkers and patterns of connectivity. Specifically, at T0 and T1, we will study the effect of tele@cognitive treatment on: i) blood biomarkers reflecting neurodegeneration, amyloid-β, tau and alpha-synuclein pathologies, neuroinflammation, synaptic function, and neuronal communication; ii) neurophysiological responses to TMS over the motor cortex. This approach will give a broad overview of the circuits modulated through telerehabilitation (tele@cognitive treatment), possibly highlighting differential effects between the groups.

Finally, the third aim will be to investigate potential cognitive, neurobiological, and neurophysiological predictors of treatment outcomes in people with CNDs who received innovative technology-enhanced telerehabilitation intervention (tele@cognitive group).

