### 2.1. Trial Design

This multicentric study is a single-blinded, randomized, controlled pilot study (RCT) involving 60 subjects with CNDs (MCI, SCCs, and PD) recruited from IRCCS Istituto Centro San Giovanni di Dio, Fatebenefratelli, Brescia, IRCCS Fondazione Don Carlo Gnocchi—ONLUS, Milan, Italy and IRCCS Centro Neurolesi “Bonino Pulejo”, Messina, Italy.

After recruitment, the subjects will be randomized into one of two parallel groups: (i) the tele@cognitive group, which will receive home-based cognitive telerehabilitation (tele@cognitive treatment); (ii) the Active Control Group (ACG), which will receive home-based unstructured cognitive stimulation. All participants will undergo a clinical, functional, neurocognitive, and quality of life assessment at the baseline (T0), post-treatment (5 weeks, T1), and at the 3-month (T2) follow-up. Neurophysiological markers (TMS) and biomolecular data will be collected at T0 and T1. The trial work plan is shown in Figure 2.

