### 2.8. Statistical Analysis

A repeated-measures analysis will be used to compare pre-treatment (T0) versus post-treatment (T1) and follow-up (T2) clinical, functional, neurocognitive, and quality of life variables for the two groups. Neurophysiological and biochemical data will be analyzed using repeated-measures ANOVAs by comparing the data recorded at T0 and T1. Statistical tests suitable for the data type will be employed to assess the differences between the groups. For continuous variables, independent *t*-tests will be utilized, while chi-square tests will be applied for categorical variables [117,118]. This analysis will verify the effectiveness of the randomization procedure, ensuring that any subsequent comparisons or evaluations between the groups are reliable and valid.

Within-group analyses will be conducted for the tele@cognitive and ACG groups to examine changes from T0 to T1 and T2. Paired *t*-tests or Wilcoxon signed-rank tests, depending on data distribution, will be employed to assess the effectiveness of the intervention over time by analyzing the variations in the collected multimodal parameters [118,119]. Furthermore, a between-group analysis will be conducted to quantitatively compare the outcomes of the two groups. Statistical tests such as independent *t*-tests, analysis of covariance (ANCOVA), or non-parametric tests will be employed, depending on the distributional assumptions and nature of the outcome variables [118,120].

In addition to these statistical analysis, predictive modeling will be implemented to identify key factors associated with treatment outcomes by integrating multimodal data from cognitive assessment, neurophysiological evaluations, biomolecular patterns, and user interaction data within a sophisticated AI framework. Given the heterogeneous nature of the data collected from multiple sources, feature selection is essential to identify the most informative features and reduce dimensionality. This step is critical to eliminate redundant or irrelevant variables and improve model performance [121]. Statistical methods such as chi-square tests and mutual information will be employed to identify significant predictors associated with positive treatment outcomes [122]. Specifically, the dataset will include baseline clinical, functional, neurocognitive, and quality of life measures, biomolecular markers, and neurophysiological parameters.

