In this context, our telerehabilitation protocol represents an ideal solution to provide intensive, long-lasting cognitive rehabilitation and to sustain treatment adherence, as well as to modify daily care routines. We expect that the findings of the present RCT will result in a recommendation of the use of a usable, safe, and effective way for changing CNDs’ behavior patterns, triggering mechanisms at the neurophysiological and neurobiological levels. The added value of this trial consists of: (i) adopting an asynchronous model of care out of the clinic, bypassing typical barriers obstructing accessibility to care structures and lowering system overburdening and costs; (ii) investigating the potential neurobiological and neurophysiological markers of the effects of the at-home tele@cognitive treatment; (iii) investigating potential cognitive, neurobiological, and neurophysiological predictors of response to the treatment, helping in the development of useful treatment pathways for patients with CNDs. It is necessary to clarify which types of patients can benefit the most from rehabilitation interventions and, above all, to pursue a more precise characterization of the specific intervention procedures. However, we acknowledge that the present RCT study has some limitations. In particular: a larger sample size might allow us to account for individual differences that could influence the efficacy of the treatment; we have not planned a cost-effective analysis of the telerehabilitation approach [168]; longer follow-up visits should be useful in following the progress of the improvement obtained after treatment. Moreover, it would have been useful to administer a scale that measured subjective experience and the attractiveness (hedonic quality) of the technology (e.g., UEQ scale; [169,170]).

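### Aim 3 models outcome in the tele@cognitive arm only, so it cannot tell factors that modify the treatment effect from factors that predict the same change under the active control

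*Protocol article*

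**What the plan says.** In the protocol article, section 1 (Introduction), the list of aims gives the third as to "analyze potential cognitive, neurobiological, and neurophysiological predictors of response to the tele@cognitive treatment". The paragraph that expands on it narrows the population to "predictors of treatment outcomes in people with CNDs who received innovative technology-enhanced telerehabilitation intervention (tele@cognitive group").

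The Discussion (section 3) gives the reason for this work: "It is necessary to clarify which types of patients can benefit the most from rehabilitation interventions". It also expects the predictors to help in developing treatment pathways.

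Section 2.8 describes the analysis: "predictive modeling will be implemented to identify key factors associated with treatment outcomes by integrating multimodal data". Feature selection, machine learning and SHAP values follow. No control contrast and no arm-by-predictor term is named for this aim. The one-arm restriction is neither repeated nor lifted.

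On what is collected, section 2.1 says "All participants will undergo a clinical, functional, neurocognitive, and quality of life assessment at the baseline (T0), post-treatment (5 weeks, T1") and again at the 3-month follow-up. It adds: "Neurophysiological markers (TMS) and biomolecular data will be collected at T0 and T1". Neither statement is limited to one arm.

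**The concern.** Response to a treatment, in the sense of who gains from it, is a difference between what happens with the treatment and what would have happened without it. In a randomised trial the control arm supplies the second part. A model fitted only to treated patients sees their outcome or change, and that mixes three things: the effect of tele@cognitive in that patient, the course the patient would have had anyway (including practice effects), and regression to the mean in a noisy baseline score.

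The comparator makes this matter more. Under section 2.5 the control group does paper-and-pencil work on the same abilities, for the same duration and frequency. A marker that predicts equal improvement under both gives no reason to choose the digital treatment, yet a one-arm analysis would report it as a predictor of response to tele@cognitive. The primary outcomes are changes from baseline (section 2.6.1) and the candidate predictors include baseline cognitive measures (section 2.8). If Aim 3 uses one of those changes as its outcome, regression to the mean applies directly.

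At stake is what Aim 3 may claim. Prognostic factors could be carried forward as guides to patient selection.

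**Working it through.** **Sample size, to fix the number of treated patients.** Section 2.3 gives a two-sided t-test, alpha 0.05, d = 0.784 and 30 per group including dropout. Its 'beta = 0.80' is read as power 0.80.
- Normal approximation: 2 × (1.960 + 0.842)² / 0.784² = 25.5, so 26 per arm.
- Exact t-test: 26.5, so 27 per arm.
- With 10% dropout (an assumption, as no rate is given): 27 / 0.90 = 30 per arm, 60 in total.

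The planned size reproduces. Aim 3 would rest on about 27 to 30 tele@cognitive patients.

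**Baseline score against change, with zero effect modification.** Let Y0 and Y1 have equal variance σ² and retest correlation ρ, and let treatment add the same amount to every patient. Then
- cov(Y0, Y1 − Y0) = −(1 − ρ)σ²
- var(Y1 − Y0) = 2(1 − ρ)σ²
- corr(Y0, Y1 − Y0) = −√((1 − ρ)/2)

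The constant shift drops out. The documents give no ρ, so a range is shown. The last two columns are simulated proportions of trials in which a one-arm correlation test gives p<0.05.

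| ρ (assumed) | corr(baseline, change) | flagged, n = 27 | flagged, n = 30 |
|---|---|---|---|
| 0.6 | −0.45 | 67% | 72% |
| 0.7 | −0.39 | 53% | 58% |
| 0.8 | −0.32 | 37% | 40% |
| 0.9 | −0.22 | 20% | 23% |

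In the same simulated data with 30 per arm, the two-arm test of the baseline-by-arm interaction is significant in 4.9 to 5.2% of trials, the nominal rate.

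**A purely prognostic marker.** Suppose a marker correlates with change equally in both arms (r assumed) and modifies nothing. With n = 27, the one-arm test flags it in about 33%, 56% and 78% of trials for r = 0.3, 0.4 and 0.5. Fisher's z confirms the middle figure: atanh(0.4) × √24 = 2.08, and Φ(2.08 − 1.96) is about 0.55. These are detections of a real association. They mislead only when called response to treatment.

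**What the two-arm analysis can deliver.** For a 50:50 binary marker there are four cells of n/2 patients, where n is the number per arm, so the interaction in SD units has SE = √(4/(n/2)).
- n = 30: SE = √(4/15) = 0.516. The interaction detectable with 80% power is 2.80 × 0.516 = 1.45 SD. Power for 0.784 SD is Φ(0.784/0.516 − 1.96) = 33%.
- n = 27: SE = √(4/13.5) = 0.544. The detectable interaction is 1.52 SD, and power for 0.784 SD is 30%.

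**The case against.** The strongest defence is that this is a pilot, that the predictors are called potential throughout, and that the Discussion itself concedes a larger sample might be needed to account for individual differences. The sentence about who benefits most states a general need; it does not promise to allocate patients to digital rather than paper treatment. The methods in sections 2.7 and 2.8 do not repeat the one-arm restriction, and a condensed article may leave model details to a fuller plan. All of that lowers the weight of the point. It does not remove it: the restriction is explicit in the statement of the aim, and a later plan with interaction terms would contradict the published aim.

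It is also fair to say that the simulations test one predictor at a time, not the planned feature selection, machine learning and cross-validation. They illustrate the mechanism and do not forecast the planned analysis. Cross-validation would not cure the problem, because a prognostic factor predicts well out of sample too.

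Three stronger readings are tempting, and the documents do not support them.
- **That Aim 3 will find only prognostic factors.** True effect modifiers would be flagged as well; the analysis just could not identify them as such.
- **That the trial discards its control data.** The control arm is used for Aims 1 and 2. It goes unused only for Aim 3 as worded.
- **That section 2.8 contradicts itself on predictors.** It speaks of "biomolecular patterns, and user interaction data within a sophisticated AI framework" and then says "the dataset will include baseline clinical, functional, neurocognitive, and quality of life measures, biomolecular markers, and neurophysiological parameters". The verb include is not exclusive, and section 2.7 lists data gathered during the programme under Aim 3, so the second sentence is at most incomplete. Platform data exist only in the tele@cognitive arm and can be modelled only there. That is a sound reason for a one-arm model of those features, but not of baseline markers collected in both arms.

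**Conclusion.** The point holds in this form: Aim 3 as stated cannot distinguish modifiers of the tele@cognitive effect from factors that predict the same change under the active control, or from regression to the mean, although its target is described as response and linked to who benefits.

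With no effect modification at all, a baseline score would be flagged as a predictor of its own change in roughly 37 to 72% of trials. This assumes 27 to 30 treated patients, a retest correlation of 0.6 to 0.8, change from baseline as the Aim 3 outcome, and one-at-a-time testing at 0.05. The article fixes neither the retest correlation nor the Aim 3 outcome. The size depends on these inputs; the inability to separate the two kinds of factor does not.

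The aim or its analysis should be changed, but this concerns an exploratory aim of a pilot and does not touch the comparisons in Aims 1 and 2.

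**What to change.** - For baseline cognitive, blood and TMS predictors, fit the Aim 3 models on both arms with arm-by-predictor terms, adjust for the baseline score of the outcome, and report the results as exploratory.
- Label any model confined to the tele@cognitive arm, including one that uses platform interaction data, as prognostic or descriptive and not as evidence of who benefits from tele@cognitive.
- Align the third aim in the Introduction, section 2.8 and the Discussion accordingly.

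If the sponsor prefers to keep only the one-arm model, the prognostic label together with removal of the response and benefit claims also resolves the point. Which outcome to model and how many markers to include are the sponsor's choice and are not part of this correction.

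No new data are needed; the change is to the wording of the aim and the specification of the models. The cost is precision. At n = 60, power is only about 33% for an interaction as large as the planned main effect, and an interaction of about 1.45 SD is needed for 80% power. The two-arm analysis asks the right question but cannot settle it, so Aim 3 cannot be confirmatory.
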